## Methods

### Objectives

The survey aims to assess adherence to AIT in a real life setting. The primary objectives are to prospectively evaluate the rate of adherence to AIT for inhalant allergies (sublingual and subcutaneous routes) and Hymenoptera venom allergy (subcutaneous) in a three year period in real life across different European countries. The secondary objectives are to identify reasons for lack of adherence and discontinuation of treatment and to explore possible reasons for differences in adherence rates in different countries and different individuals.

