### Participant selection and procedure

The survey population consists of adults with IgE mediated respiratory allergies or Hymenoptera venom allergy who will be starting AIT (either SCIT or SLIT) according to accepted clinical standards of practice.

The inclusion criteria were set as: male or female, 18 years of age or over (no upper age limit) and being eligible for immunotherapy to inhalant allergens or Hymenoptera venoms. The exclusion criteria were previous AIT treatment at any time and any contraindications to receiving immunotherapy according to European standards of practice.

Each participating centre coordinator identified any potential participants and assessed whether they met these criteria. In order to enrol a participant, an online enrolment questionnaire was required to be completed by the physician. This form includes information about the participant, details about their allergies and treatment.

For each participant an online follow up adherence form will be completed by the local physician every 4 months. This adherence follow-up form includes questions regarding the number of missed doses, phase of the treatment at the time and any possible reasons for missed doses. The last adherence follow-up form will be completed at 36 months from AIT initiation.

In case of participant withdrawal, a discontinuation online form will be completed. This includes questions including the timing and any identified reasons for stopping AIT.

The enrolment period opened in December 2012 and closed in February 2014.

The study timeline is shown in Figure 1.

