### Statistical analysis

#### Sample size estimation

Different proportions of expected drop-out are reported in Table 3. Confidence intervals are computed under this expected proportions assuming 1,000 patients will be recruited.

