#### Data analysis

The primary objective will be summarised as a proportion ± confidence interval 95% (binomial method).

The influence of potential predictors on lack of adherence or discontinuation from the therapy will be explored using a logistic regression. The effect of the hierarchical structure of the data (participants *nested in* centres *nested in* countries) on the results will be eventually explored using multilevel analyses.

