## Discussion

Adherence to AIT is an area that requires further investigation as the data currently available is mainly from clinical trials with only a limited number of real life studies and even fewer prospective studies [33,48-50].

This project will provide an insight into this important issue. It will enable an estimation of the rate of adherence to AIT in daily clinical practice for respiratory allergic disorders and Hymenoptera venom allergy. Furthermore, it will allow identification of possible reasons for lack of adherence and discontinuation of treatment. This will provide useful information for changing or modifying clinical behaviours and attitudes towards immunotherapy, in order to improve adherence wherever possible.

The main strengths of this survey are:As a multi-country survey a large number of participants will be recruited and adherence of AIT in a large part of Europe will be assessed. Given the significant number of participants included, the conclusions drawn are more likely to be applicable to a wider population. At the same time, it will enable identification of inter-country differences regarding the use of different routes of administration and reasons for discontinuation.Sharing the same methodology by all participating centres will allow for more reliable and comparable results.In addition to AIT for respiratory allergies, adherence to Hymenoptera venom immunotherapy will also be addressed in this survey. Possible contributing factors leading to lack of adherence or discontinuation will be explored in detail such as extract used, schedule, responsible insect, severity of index reaction and any side effects to AIT.

The use of online survey software has enabled us to make this survey a reality and reach clinicians in 8 different countries. Following the end of the enrolment period, over 1,350 participants have now been enrolled by 45 centres. The main allergens for which participants are having AIT include grass pollens 33.9%, house dust mite 32.3% and 15.3% Hymenoptera venoms. Preliminary one-year follow up data shows that 11.1% of participants have missed on average 2 doses in 4 months whilst less than 2% of participants have discontinued treatment.

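### The committed predictor analysis is a single-level logistic regression, which can overstate the evidence for predictors that vary mainly between centres or countries; the clustered model should lead

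*Protocol article*

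**What the plan says.** - **Predictor model.** Under Data analysis, the influence of potential predictors on "lack of adherence or discontinuation from the therapy will be explored using a logistic regression". No term for centre or country is named.
- **Clustering.** The next sentence reads "The effect of the hierarchical structure of the data", spells out the nesting of participants in centres in countries, and continues "on the results will be eventually explored using multilevel analyses". Whether this means in due course or possibly, the section gives no trigger and does not say which result stands if the two analyses disagree.
- **Objective served.** Under Objectives, a secondary aim is to "explore possible reasons for differences in adherence rates in different countries and different individuals". The Discussion lists the identification of differences between countries as a strength.
- **Size.** The Discussion reports "over 1,350 participants have now been enrolled by 45 centres". Survey design names eight countries.
- **Unit.** Table 3 counts adherent patients out of 1,000, and the primary result is one proportion with a binomial interval. Both point to one outcome per participant.

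**The concern.** A single-level logistic regression treats all participants as independent. If adherence is correlated within centres or countries, a predictor that is constant within a cluster carries far less information than the number of participants suggests. Its standard error is then too small and its p-value too optimistic.

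The article itself gives reasons to expect some correlation. Questionnaire design says that follow-up of SLIT patients differs between countries and that supplementary sources, such as pharmacy records or telephone contact, depend on national practice. Recorded adherence could therefore differ by country even if behaviour did not. The abstract says that the countries were chosen partly for differences in route of administration.

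At stake is the secondary objective on country differences. A national or centre practice could be reported as a reason for poor adherence on evidence that is really about eight or 45 units. The Discussion expects the findings to inform changes in clinical practice, so overstated precision would have consequences even in exploratory work.

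**Working it through.** **1. The plan's own figures.** Table 3 is the only statistical calculation in the article, and it is made "assuming 1,000 patients will be recruited". The exact (Clopper-Pearson) interval for 800 of 1,000 is 77.38% to 82.44%, against the stated 77.4% to 82.4%. All eight rows reproduce to 0.1 point (the 75% row once its limits are put in ascending order). These intervals assume independent patients. No power or significance level is given for predictors.

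**2. Inputs.**
- From the article: about 1,350 participants, 45 centres, 8 countries. Means are 1,350/45 = 30 per centre and 1,350/8 = 168.75 per country.
- Assumed: two-sided 5% tests, the ICCs below, 80% adherence (one of the Table 3 rows) and equal centre sizes.

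**3. Simple bound, one ICC for all pairs in a cluster.** Design effect DE = 1 + (m − 1) × ICC. True error of a nominal 5% test = 2 × [1 − Φ(1.96/√DE)].

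| ICC | Centre-level, m = 30 | Country-level, m = 168.75 |
|---|---|---|
| 0.005 | DE 1.15, error 6.7% | DE 1.84, error 14.8% |
| 0.01 | DE 1.29, error 8.4% | DE 2.68, error 23.1% |
| 0.02 | DE 1.58, error 11.9% | DE 4.36, error 34.8% |
| 0.05 | DE 2.45, error 21.1% | DE 9.39, error 52.2% |

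The country column is too severe if the ICC is read as a within-centre value. Patients in different centres of one country share only the country component.

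**4. Variance split between centre and country.** Simulation of the single-level Wald test under the null: 8 countries, 45 centres of 30, normal random intercepts on the logit scale, a binary predictor, 2,000 runs per setting.

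| Latent ICC, centre + country | Patient-level predictor | Centre-level | Country-level |
|---|---|---|---|
| 0 + 0 | 4.9% | 5.1% | 5.1% |
| 0.01 + 0.005 | 5.3% | 7.1% | 13.1% |
| 0.02 + 0.01 | 4.5% | 9.6% | 19.7% |
| 0.05 + 0.02 | 4.3% | 15.9% | 32.3% |

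The Monte Carlo standard error is at most about √(0.323 × 0.677/2,000) = 1.0 point.

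**5. Hand check of the country column.** A latent ICC ρ corresponds to a variance of (π²/3) × ρ/(1 − total). Multiplying by 0.8 × 0.2 = 0.16 gives the approximate ICC on the yes/no scale. Let a be this ICC for centre and b for country. For a country-level predictor, DE ≈ 1 + 29(a + b) + (168.75 − 30)b.
- 0.01 + 0.005: a = 0.0053, b = 0.0027, DE ≈ 1.60, error about 12%.
- 0.05 + 0.02: a = 0.0283, b = 0.0113, DE ≈ 3.72, error about 31%.

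These agree with the simulated 13.1% and 32.3%. They also show that the errors in step 4 fall below those in step 3 for two reasons: the variance is split, and the ICC is defined on the latent scale.

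**The case against.** The strongest reply is that the plan already sees the problem. It names the correct hierarchy and a suitable method, calls the predictor work exploratory, and states no significance level for it. Details of the multilevel model may sit in a fuller plan that is not shown. That limits the point, but does not remove it: the article states an order of analyses, and the model that ignores clustering is the one it commits to.

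Three stronger readings are tempting, and the article does not support them.

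- **That centre-level and country-level predictors will look significant far too often.** No ICC is given, so the inflation is conditional. At a centre ICC of 0.01 or less, the centre-level error is at most 8.4% even under the simple bound. The 23% to 52% for country-level predictors (ICC 0.01 to 0.05) requires one ICC to apply to every pair of patients in a country.
- **That the hierarchy is wrong because it leaves out the repeated forms.** It is true that "an online follow up adherence form will be completed by the local physician every 4 months", so there can be up to 36/4 = 9 forms per participant. But the unit appears to be the participant, and a hierarchy that starts there is then complete. A missing form level would also not cause inflation at centre or country level.
- **That eight countries are too few for the plan's country random effect.** The plan specifies no such effect. The small number of countries only affects how the remedy is chosen.

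It is also fair to say that route, setting, funding and follow-up arrangements are recorded for each participant. The article supports variation between countries for route and for SLIT follow-up, but not expressly for funding or setting. Confounding of individual predictors by country would arise only if country were left out of the model, and the article lists no covariates.

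**Conclusion.** The concern holds in a limited form. The only predictor model that the article commits to ignores a clustering it acknowledges, while a secondary objective concerns country differences. Over the assumed latent ICCs (0.01 + 0.005 to 0.05 + 0.02), a nominal 5% test has an error of about 7% to 16% for a centre-level predictor and 13% to 32% for a country-level one. A predictor that varies both within and between centres should lie between these figures and 5%. Patient-level predictors unrelated to centre are little affected.

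The size rests on the assumed ICCs and significance level, on 80% adherence and on equal centre sizes. Unequal sizes would increase the inflation. The primary objective is not at issue here. This is a cheap improvement to a stated method, not an error that invalidates the survey.

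**What to change.** - State that the outcome in the predictor analysis is one value per participant. Make a logistic model with a random intercept for centre and country as a fixed effect the main analysis.
- Keep the ordinary logistic regression as a sensitivity analysis, and say that the clustered model stands if the two disagree.
- Present explanations of differences between the eight countries descriptively, without participant-level p-values. With country as a fixed effect, a predictor that is constant within country cannot be separated from country in any case.
- Add a form-level model, with a participant level, only if the 4-monthly form is to be the unit of analysis. It is optional otherwise. It would need more than a reordering, because the form as described records missed doses and not prescribed doses.

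Cost: no new data, since Data management says that each participant's code already contains the country and centre codes. Intervals for centre-level predictors will be wider, and there is a little more modelling work.

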### Regulatory and ethical obligations

European Union and specific country ethics and regulatory requirements, including data protection, will be followed. Each National survey co-ordinator will be responsible for addressing the corresponding ethics committee and local regulatory requirements.

### Survey progress

The PASTE co-ordinators are responsible for the proper running of the survey. They are in regular contact with National co-ordinators and individual centres when required. Meetings, conference calls and newsletters are used as a method of updating progress. Following enrolment, the next task is to ensure timely completion of the 4-monthly follow up forms and any discontinuation forms for all the enrolled participants. The data will then go through a further clearing process, followed by data analysis.

## Discussion

Adherence to AIT is an area that requires further investigation as the data currently available is mainly from clinical trials with only a limited number of real life studies and even fewer prospective studies [33,48-50].

This project will provide an insight into this important issue. It will enable an estimation of the rate of adherence to AIT in daily clinical practice for respiratory allergic disorders and Hymenoptera venom allergy. Furthermore, it will allow identification of possible reasons for lack of adherence and discontinuation of treatment. This will provide useful information for changing or modifying clinical behaviours and attitudes towards immunotherapy, in order to improve adherence wherever possible.

The main strengths of this survey are:As a multi-country survey a large number of participants will be recruited and adherence of AIT in a large part of Europe will be assessed. Given the significant number of participants included, the conclusions drawn are more likely to be applicable to a wider population. At the same time, it will enable identification of inter-country differences regarding the use of different routes of administration and reasons for discontinuation.Sharing the same methodology by all participating centres will allow for more reliable and comparable results.In addition to AIT for respiratory allergies, adherence to Hymenoptera venom immunotherapy will also be addressed in this survey. Possible contributing factors leading to lack of adherence or discontinuation will be explored in detail such as extract used, schedule, responsible insect, severity of index reaction and any side effects to AIT.

The use of online survey software has enabled us to make this survey a reality and reach clinicians in 8 different countries. Following the end of the enrolment period, over 1,350 participants have now been enrolled by 45 centres. The main allergens for which participants are having AIT include grass pollens 33.9%, house dust mite 32.3% and 15.3% Hymenoptera venoms. Preliminary one-year follow up data shows that 11.1% of participants have missed on average 2 doses in 4 months whilst less than 2% of participants have discontinued treatment.

Participants will be followed for a total of 3 years. At that point we will be able to analyse all the data and disseminate the findings to the allergy community in order to benefit from this information and depending on the outcomes consider targeting strategies and ways of improving adherence.

## Abbreviations

AIT: Allergen immunotherapy
EAACI: European Academy of Allergy and Clinical Immunology
PASTE: Prospective adherence to specific immunotherapy in Europe
SCIT: Subcutaneous immunotherapy
SLIT: Sublingual immunotherapy
SSL: Secure sockets layer
